#### Plans to provide access to the full protocol, participant-level data, and statistical code {31c}

The detailed information of the study is accessible in the study registry clinicaltrials.gov. After publication, full access to the participant level data and statistical code is planned by the Research Institute of Social Medicine, Epidemiology and Health Economics of the Charité University Hospital Berlin.

### Oversight and monitoring

#### Composition of the coordinating center and trial steering committee {5d}

The coordinating center is located at the research institute (Institute for Social Medicine, Epidemiology and Health Economics) at the Charité University Hospital in Berlin and comprises the principal investigator, the coordinating physician, 4 acupuncturists, 2 study nurses, the data monitoring and management team, and the statistical advisor. The steering committee consists of the director of the research institute and the principal investigator. Serious adverse events are directly reported to this committee within 24 h of notification.

#### Composition of the data monitoring committee, its role, and reporting structure {21a}

A data monitoring committee was not considered as this study adopts a low-risk intervention, and an interim analysis is not planned in this study.

#### Adverse event reporting and harm {22}

A short description of the patients’ general wellbeing and any adverse events is documented at each of the 12 acupuncture sessions. Serious adverse events are noted on a separate form and will be reported to the principal investigator within 24 h. Known potential side effects are intensified tingling at the beginning of treatment (in patients with underlying tingling sensation); local pain, local infection, or bruising at the needle site; and orthostatic reaction after rising from the reclined position.

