### Objectives {7}

The aim of this randomized controlled clinical study is to assess the effectiveness and safety of acupuncture in addition to routine care compared to routine care alone for the treatment of symptomatic DPN with respect to the postulated underlying TCM-patterns in terms of the impact on overall symptoms, pain, neurophysiological outcomes, the use of analgesics, sleep disturbances, specific and general quality of life, and adverse events.

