## Methods: participants, interventions, and outcomes

### Study setting {9}

This study is being conducted in Germany. The main recruiting center is located in Berlin at the Charité University Hospital, and another recruiting center is located in Hamburg in a research and treatment center for traditional Chinese medicine. The overall study duration per patient is 24 weeks. After randomization at baseline, the patients in the acupuncture group will undergo 12 treatment sessions in addition to routine care during the first 8 weeks of the study, followed by 16 weeks of follow-up. In the control group, all patients will continue to receive routine care and undergo several study follow-up examinations during the first 16 weeks. In this control group, patients are on a waiting list for the acupuncture treatment, which will be started at week 16 and continued until the final follow-up at week 24 using the same acupuncture treatment protocol being performed in the other study arm (see Fig. 1 and Table 1).

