**Optional points depending on the following Chinese medicine diagnoses**	
Cold invasion into meridians	Moxa on EX-LE-10 Bafeng, KI 3
Deficiency of qi and xue	ST 36, GB 39, ST 41 (in pronounced sensory ataxia)
Qi-stagnation and blood stasis	GB 34, GB 40, SP 4
Wind and phlegm block channels	ST 36, SP 9, SP 4
Phlegm and heat block channels	SP 9, SP 10, GB 40, KI 7

Furthermore, at least 2 of 10 facultative acupuncture points will be selected according to the patient’s individual constitution and disease pattern following the diagnostic principles of Chinese medicine {11b}. The acupuncture points used in a session will be documented each time. A diagnosis of traditional Chinese syndrome at baseline is mandatory, and the diagnosis will be documented. Patients will lie down in supine position. Needles will be inserted perpendicularly and stimulated only in the beginning to achieve a DeQi sensation and then will be left in place without further stimulation for 20–25 min.

The duration of 12 acupuncture sessions within one treatment cycle with 1–2 sessions per week and between 20 and 30 min per session is supported by common textbooks for acupuncture and taught in acupuncture schools internationally. The needle length and diameter will be chosen according to the anatomical location and constitutional picture. If numbness is present, superficial puncture with a sharp needle will be carried out at the Bafeng points, and tiny amounts of blood will be released twice during the treatment period. In both groups, moxibustion is allowed and will be applied by using a common moxibustion TDP- lamp (Phoenix Bio TDP CE005) exclusively at the feet over 15 min at 20 cm distance to the toes, in case of cold and numb feet. Since the focus is on body acupuncture, we excluded auricular acupuncture strategies.

The patients in the control group will not receive acupuncture treatment for a period of 16 weeks after randomization. During this period, the patients in the control group will participate in follow-ups only with the use of diaries and questionnaires. After 16 weeks, the patients in this group will receive the same acupuncture treatment according to the principles described above.

The patients in both groups will be allowed to continue routine care medication (if applicable), which will be adapted as needed during the study.

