In addition, the patients will be requested to complete patient diaries following a daily schedule, which will include recording on-demand medication use, a weekly assessment of the average VAS score of pain, and the overall number of DPN-related complaints during the first 8 weeks and at weeks 15 to 16 and 23 to 24.

The neurophysiological parameters will include measurements of the sural nerve. This nerve is pathognomonically affected in diabetic neuropathy and is used to monitor peripheral neuropathy. The nerve conduction velocity and amplitude of sensible action potentials will be measured with a novel point-of-care nerve conduction device (POCD) produced by NeuroMetrix™, Texas. This device is used in the DPNCheck®, which provides accurate, cost-effective, and quick screening data for the diagnosis and monitoring of diabetic peripheral neuropathy (DPN). With a 10-s period of measurement, this device can provide the numeric values of velocity (m/s) and amplitude (μV). This device has been validated in several studies as an accurate screening and monitoring instrument for DPN and the evaluation of the risk of diabetic foot [25–27].

TCM-related indexes as outcomes are not used in this trial.

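### Adverse events are scheduled for recording only at acupuncture sessions, so the planned safety comparison with routine care rests on unequal ascertainment of non-serious events before week 16

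*Protocol article*

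**What the plan says.** Objectives {7} states that the trial is "to assess the effectiveness and safety of acupuncture in addition to routine care compared to routine care alone", and adverse events close the list of endpoints. Adverse event reporting and harm {22} gives the recording procedure: a short note on general wellbeing and "any adverse events is documented at each of the 12 acupuncture sessions". Serious events go on a separate form and reach the principal investigator within 24 hours.

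On the control arm, Study intervention {11a} says "The patients in the control group will not receive acupuncture treatment for a period of 16 weeks after randomization" and then "During this period, the patients in the control group will participate in follow-ups only with the use of diaries and questionnaires". Study setting {9} describes the same period differently: controls "undergo several study follow-up examinations during the first 16 weeks".

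Outcomes {12} describes a diary "which will include recording on-demand medication use", a weekly pain VAS and the overall complaints. It covers the first 8 weeks, weeks 15-16 and weeks 23-24, and no adverse-event item is listed. The same section states, without method, timing or limit to one arm, that adverse events, dropouts and withdrawals will be documented.

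**The concern.** A between-arm comparison of adverse events is interpretable only if both arms are asked in the same way and about equally often. Here the one scheduled procedure is attached to a treatment visit that one arm does not have during the comparison period. Patients asked at every session will report minor and background events that patients followed by post may never mention. An excess in the acupuncture arm could then reflect more questioning rather than more harm. Non-serious events that appear after the last session would also have no scheduled occasion on which to be recorded, although follow-up runs to week 24.

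The Discussion says the results will bear on whether acupuncture is an effective and safe option, and section {21a} dispenses with a data monitoring committee, partly because the intervention is considered low-risk. The adverse-event data collected in the trial therefore carry the safety conclusion.

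**Working it through.** The article states no safety figure to reproduce, and the sample-size calculation does not bear on this point. The check is a count of recording occasions, followed by an illustration of the bias.

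**1. Scheduled adverse-event occasions described in the article**

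| Period | Acupuncture arm | Control arm |
|---|---|---|
| Weeks 0-8 | 12 (one per session, {11a} and {22}) | none described |
| Weeks 8-16 | none described | none described |
| Weeks 16-24 | none described | at the sessions of the deferred course |

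Up to week 16, the last point at which controls have had routine care alone, the count is 12 versus 0.

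**2. Does the uncertainty about control follow-up change this?** Suppose Study setting {9} is followed, that controls are examined at weeks 8 and 16 (the times given in Outcomes {12}), and that the examiner asks about adverse events, which the article does not say. The acupuncture arm would have the same two examinations. The count becomes 12 + 2 = 14 versus 2. The imbalance is smaller but remains.

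**3. Effect on the comparison.** Let p be the true risk of a non-serious event, equal in both arms, and let c_A and c_C be the proportions of patients with an event whose event is recorded.

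- Recorded risks: p × c_A and p × c_C
- Apparent risk ratio: c_A / c_C, which does not depend on p
- Apparent risk difference: p × (c_A − c_C)

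None of these inputs is in the article. Assume c_A = 0.90, c_C = 0.50 or 0.25, and p from 10% to 30%:

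| p | c_C | Recorded, acupuncture | Recorded, control | Difference (points) | Ratio |
|---|---|---|---|---|---|
| 10% | 0.50 | 9.0% | 5.0% | 4.0 | 1.8 |
| 10% | 0.25 | 9.0% | 2.5% | 6.5 | 3.6 |
| 20% | 0.50 | 18.0% | 10.0% | 8.0 | 1.8 |
| 20% | 0.25 | 18.0% | 5.0% | 13.0 | 3.6 |
| 30% | 0.50 | 27.0% | 15.0% | 12.0 | 1.8 |
| 30% | 0.25 | 27.0% | 7.5% | 19.5 | 3.6 |

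With equal capture (c_C = 0.90) the ratio is 1.0 and the difference is 0. With 110 randomized 1:1, 55 per arm, the row with p = 20% and c_C = 0.50 corresponds to 55 × 0.18 = 9.9 versus 55 × 0.10 = 5.5 patients with a recorded event, although the true risk is the same.

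**The case against.** The strongest reply is that saying events are recorded at sessions does not say they are recorded nowhere else. Outcomes {12} promises adverse-event documentation for the whole trial, directly after the assessments at baseline and weeks 8, 16 and 24. Serious events have a separate form in {22} and go to the steering committee under {5d}, in both cases without reference to arm or session. Study setting {9} gives controls examinations before week 16. The diary list need not be complete, the assessment schedule (Fig. 1, Table 1) is not visible in the text at hand, and a journal article may leave form content to the full protocol. Any bias would also run against acupuncture.

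Much of this stands. A reader might infer that controls have no adverse-event ascertainment at all before week 16. The article does not support that, because of the general statement in {12} and the separate route for serious events. A reader might also put a p-value on the artefact: 6/55 versus 0/55 gives a two-sided Fisher p of 0.027. That assumes full capture in one arm, none in the other and a background risk that is not in the article. It is an upper bound and depends on rounding, since 10% of 55 is 5.5 and 5/55 versus 0/55 gives about 0.057.

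The reply does not remove the narrower point. The article does not merely omit a method. It gives one, in the section devoted to harms, and ties it to a procedure that only one arm undergoes during the comparison. The general statement in {12} supplies no method or timing that would restore the balance. The serious-event route covers serious events only, and under {5d} its clock starts at notification.

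**Conclusion.** The point holds for non-serious events. As described, ascertainment is unequal between the arms up to week 16 (12 scheduled occasions versus none described), and the article names no scheduled occasion in the acupuncture arm after its last session. This does not fit the stated comparison of safety with routine care alone.

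The likely direction is an overstated excess in the acupuncture arm. The size cannot be fixed from the article. The spurious risk ratios of 1.8 and 3.6 rest on equal true risk, an assumed 90% capture under acupuncture and assumed control capture of 50% or 25%. If the full protocol already asks both arms the same question at the same times, what remains is to say so in the article.

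The primary efficacy analysis is untouched, and all other analyses are declared exploratory. This is a correction worth making for the safety conclusion, not a threat to the trial's main result.

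**What to change.** 1. Add one identical adverse-event question to the existing diaries and to the mailed questionnaires at weeks 8, 16 and 24 in both arms. The diaries do not cover weeks 9-14, so the week 16 questionnaire should ask about the whole interval since week 8.
2. Base the between-arm safety comparison on this common source over weeks 0-16. After week 16 controls receive acupuncture, so a comparison with routine care alone is no longer available.
3. Report events recorded at sessions descriptively, for acupuncture recipients only.
4. Reconcile Study setting {9} with Study intervention {11a} on whether controls are examined before week 16 or followed by diaries and questionnaires only.

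The cost is one extra item in instruments that already reach both arms, plus a minor amendment. Patients already past these time points would be covered only partly or not at all. Trial status reports 62 included by Jan 5, 2021, which leaves 110 − 62 = 48 still to be included at that date. The date of the change must be reported, with the number of patients asked under each procedure.

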#### Frequency and plans for auditing trial conduct {23}

The project management group meets every week to discuss the trial development and upcoming issues in both participating centers. The study documents and facilities were audited in October 2019; the auditor is independent from the research institute of the Charité University Medicine Hospital; no major findings were documented. All study procedures have been described in SOPs to maintain the quality of the trial conduct.

#### Plans for communicating important protocol amendments to relevant parties (e.g., trial participants and ethical committees) {25}

All amendments to the protocol are communicated via weekly research team meetings; the center in Hamburg is informed via E-mail, telephone conference, and a personal visit regarding any changes to the protocol. All amendments must be presented to the local ethical board in Hamburg for a positive vote as required by the federal organization of the ethical boards in Germany. If further changes are made, they will be communicated in the same way.

#### Dissemination plans {31a}

The participants are allowed to ask for the results of their individual electrophysiological examinations of the nervus suralis as soon as they completed their final study procedures. The trial participants will be informed of the general outcome of the study via email as soon as the results have been published in a peer reviewed journal. The Veronica and Karl Carstens foundation, who provided a research grant to [name], will publish the results and a link to the publication on their website.

## Discussion

This study involving type II diabetic patients who suffer from diabetic neuropathy investigates whether 12 sessions of acupuncture along with routine care can improve symptoms in the lower limbs compared to the use of routine care alone. To the best of our knowledge, the ACUDPN study is the first clinical study to investigate the effectiveness of acupuncture treatment for DPN compared to routine care alone in a multicenter two-armed clinical trial. Due to the variety of DPN-related neurological complaints, the effectiveness of acupuncture is not easily investigated in this condition. We decided to test the overall VAS-DPN-related complaints to account for not only pain but also tingling and numbness as these symptoms can also seriously affect DPN patients. However, to allow for the differentiation of the subdimensions of neuropathic pain, the NPSI will be used in this study as a secondary outcome parameter.

The neurophysiological follow-up is limited to measurements of the sural nerve with the new handheld device DPNCheck®. The conductivity of the sural nerve is an established indicator of the severity of DPN and can be assessed noninvasively. The advantage of the new device is the provision of numeric values, leaving no room for the interpretation of curves as is usually performed in conventional manual evaluations of the measurement.

The main inclusion criteria have been applied in other clinical studies before evaluating the efficacy of acupuncture on the basis of nerve conduction measurements [11, 13, 16]. Therefore, in addition to using a modified and extended inventory of tools, our study fulfills the confirmatory demands suggested by previous research.

Regarding the weak evidence of an acupuncture effect on DPN in prior sham-controlled trials [28], most trials suffered from methodological shortcomings; therefore, a repetition of the question in an open-label trial of higher methodological quality comparing routine care with acupuncture to routine care alone seems well justified. Therefore, we decided to clarify primarily whether acupuncture has overall effects on DPN in a routine care study. As a second step, a sham-controlled trial should be designed to determine whether acupuncture has specific needling-related effects on DPN.

Acupuncture practiced according to the principles of Chinese medicine is an individualized therapy [29]. In the ACUDPN study, we use a semi-standardized treatment protocol that is similar to the treatments applied in several other previous studies, including the ART and the ACUSAR studies [30–34].

Compared to previous studies investigating acupuncture for the treatment of DPN, the ACUDPN study uses additional acupuncture sessions and applies a more rigorous methodology, including validated questionnaires and neurophysiological parameters, with a longer follow-up period to assess the long-term effects.

In conclusion, the results of the ACUDPN study will have an impact on the decision of whether acupuncture might be considered an effective and safe therapeutic option for the treatment of DPN and whether acupuncture can exert neuroregenerating effects.

## Trial status

Protocol Version 1.0_22102018. Recruitment started in February 2019. Number of included patients on Jan 5, 2021: 62. Planned end of the recruitment period: Oct 2021 (due to the delay caused by the coronavirus pandemic) with inclusion of the last patient; planned end of study: March 2022.

## Abbreviations

ACUDPN: Acupuncture in Diabetic Peripheral Neuropathy
ACUSAR: Acupuncture in Seasonal Allergic Rhinitis
ART: Acupuncture randomized trial
DPN: Diabetic Peripheral Neuropathy
DPNPI: Diabetic Peripheral Neuropathic Pain Impact
NCV: Nerve conduction velocity
NCS: Nerve conduction study
NDS: Neuropathy Deficit Score
NPSI: Neuropathic Pain Symptom Inventory
NSS: Neuropathy Symptom Score
PGIC: Patient Global Impression of Change
SES: Schmerzempfindungs Skala -German Emotional Pain Perception Scale
SF-12 QoL: Short-Form-12 Quality of Life Questionnaire
cTNS: Clinical Total Neuropathy Score
VAS: Visual Analog Scale
